# Ansökan om etikprövning – *Bilaga 3*

## Forskningsplan avsedd för fackmän

### Background

Depression, social anxiety disorder, and panic disorder are prevalent and lead to individual suffering and negative societal consequences (1). Cognitive behavioral therapy (CBT) has strong empirical support but still, 30-60% of patients end up as non-responders. Personalized medicine aims to identify patients that are suitable for a certain treatment or need a certain adaption within a treatment. All types of data can be used for the purpose of identifying patient needs and guide clinical decisions (2).

A 'Learning Machine' is a combination of a number of machine learning/artificial intelligence (AI) algorithms. It can use a multitude of data sources and learn from a large set of example cases, for example patients receiving a treatment, and then applying what it has learnt to predict outcome for a new patient. Machine learning/AI has recently been introduced in psychiatric research, for example in suicidality prediction and using fMRI to distinguishing CBT responders from non-responders (3), in analysis of free speech to predict later development of psychosis (4), to estimate long-term severity of depression (5), and to identify patients likely to respond to a specific antidepressant (6).

A vast majority of traditional prediction research focuses on finding factors that predict for example treatment outcome. The strength of a Learning Machine is that it combines many predictors, also rather weak ones, and makes predictions on the individual level. However, to actually become useful in regular care, two criteria must be fulfilled: (1) the prediction for a patient needs to be strong enough to base important clinical decisions on and (2) the prediction must be presented to the clinician in a way that is easy to grasp, acceptable and suitable within the clinical context. So far, not even studies using AI/machine learning to classify psychiatric patients have actually taken the next step and developed a decision support tool (DST), i.e. a system presenting predictions for therapists and give them guidelines on how to interpret and act on these predictions, and then tested its ability to increase quality of care.

Internet-based Cognitive Behavioral Therapy (ICBT) with brief therapist support emerged in the late 90-ies and has rapidly received empirical support for a wide range of conditions (7). The primary investigator in this project has since 1999 been a pioneer in evaluating and implementing ICBT in regular care and Sweden is one of the leading countries in this field, where the Internet Psychiatry Clinic ([www.internetpsykiatri.se](http://www.internetpsykiatri.se)) in Stockholm is a very successful implementation. ICBT is a highly suitable context for developing and testing a DST powered by a Learning Machine. It collects a lot of data, is highly standardized and thus more predictable, and is easy to integrate with a digital treatment platform.

The idea of achieving strong enough predictions to base clinical decisions on might seem like a utopia, even with the computational power of a Learning Machine. If the goal is to use baseline data to match a patient to a treatment, previous failures to show coherent results

are indeed discouraging (for example 8, 9). However, the picture becomes brighter when data from the initial parts of treatment is added. Continuous monitoring of symptoms has been used to detect patients at risk of being a non-responder in a more reliable way than psychotherapist's own predictions (10), and has led to fewer failed treatments (11). Using early weekly symptom ratings in ICBT has also been shown to be successful in predicting treatment failures (12).

A predictive DST combined with a treatment that has the capability of quickly adapting to the clinical needs of an identified, probable non-responder thus has the potential to avoid treatment failures and increase overall response rates. We call this method an Adaptive Treatment Strategy. Besides the above mentioned advantages in integrating ICBT and a decision support tool, ICBT provides good opportunities to increase the "treatment intensity" during treatment since it starts from a low intensity (10-15 minutes of therapist time each week) which can be increased by for example intensifying therapist support and/or provide it via telephone or add new treatment modules.

Personalized medicine is the science of individualized care and aims to identify which patient would benefit from which type of care. Internet-based Cognitive Behavioral Therapy (ICBT) in combination with Artificial Intelligence (AI) and machine learning provides an opportunity to start implementing personalized medicine in psychiatric care. Previous studies using AI/machine learning within the context of personalized medicine have only evaluated the predictive capacity, without actually testing if the categorization of patients can be transformed into a tool that results in better treatments.

Continuous monitoring of symptoms to some extent predicts outcome in psychological treatment. We have previously used an Adaptive Treatment Strategy in a randomized clinical trial to identify patients in ICBT for insomnia at risk of being non-responders and considerably increased positive outcome for those by providing enhanced ICBT (13). However, the semi-manual classification routine consumed valuable therapist time and its predictive power leaves room for improvement. A so called Learning Machine combines a range of AI/machine learning algorithms to use a wide range of data sources to learn from a large set of examples (patients) and applies this knowledge on a new patient, in order to for example predict final outcome (14). Learning Machines can often outperform traditional prognostic methods but so far their actual usefulness in a clinical setting have not been tested in a RCT.

In an ongoing collaboration between the Internet Psychiatry Clinic, KI, and KTH we have used 5500 historical patients having received ICBT for depression, social anxiety or panic disorder to train a Learning Machine to use data from baseline and early on in treatment (primarily week 1-4) to predict a patient's end state. The primary outcome we have predicted is patients being non-responders or deteriorators, since this is the most important group to intervene on if using an Adaptive Treatment Strategy. This has then been used as a base for a DST.

During the spring of 2020 we have developed a first version of this DST giving ICBT therapist at the Internet Psychiatry Clinic feedback on their patients' predicted end state. We involved the users (therapists) in the development process and in a pilot trial with actual patients and evaluated its acceptability and perceived usefulness before finalizing its design. This pilot

study needs to be followed up by a randomized controlled trial to evaluate the clinical effects of this tool.

## Aim & Research questions

The overall aim is to test the actual clinical benefits of an AI-based DST being used as the core component in a so called 'Adaptive Treatment Strategy' and to evaluate how the DST affects therapists and their patients with depression, social anxiety, or panic disorder during 12 weeks of ICBT. The effect of this is expected to be fewer treatment failures, larger overall reductions of symptoms, more efficient use of therapists' time, and less need for further treatment.

More specifically, the project aims to evaluate ICBT with a DST for depression, panic disorder and social anxiety (the DST arm) compared to ICBT using only a traditional, detailed therapist manual and making, but not showing, predictions (the TRAD arm) concerning the following areas:

1. The DST will result in larger symptom reductions (Primary Hypothesis) and fewer actually failed treatments, (i.e. being neither a responder nor a remitter), among patients predicted to fail compared to TRAD.
2. The overall reduction of the patient's disorder specific symptoms and number of failures will be larger for DST than for TRAD.
3. The DST will make therapists more time efficient, defined as the ratio of 'decrease in symptoms / therapist time spent on patient' compared to TRAD.
4. The DST will have superior outcomes compared to TRAD on the following:
  - a. Level of everyday functioning
  - b. Health related quality of life
  - c. Treatment adherence/compliance
  - d. Patient satisfaction
  - e. Number of Adverse Events experienced by the patient
  - f. Need for further treatment
  - g. Sudden symptom changes
5. For therapists, the DST will, compared to TRAD and the therapist manual used there, result in:
  - a. A more positive experience of using the DST / the therapist manual, including higher perceived helpfulness and credibility and the overall experience of supervision, clinical routines, and guidance of their clinical decisions
  - b. More and longer contacts (messages, phone/video calls) with patients, more treatment adaptations made, and more detailed advice and feedback for those patients predicted to fail.
  - c. The same level of contacts, adaptations and details for patients predicted to succeed.

## Method

### Design

This study is designed as a triple blind randomized controlled trial, where half of the therapists allocated to DST and the other half to TRAD. The therapists and patients will be blind to what group they are allocated to and the post-treatment assessors will also be blind to what group the patients belong. The therapists and patients will know that they are

randomized, but will be informed that the study concerns two different types of treatment structure and supervision, and will thus be blind to the true purpose of randomization. After randomization both groups will be informed that they are in the experimental group to further ensure that they are blind, therapists in TRAD will be informed that the other arm receives a much simpler therapist manual and half the amount of supervision. The trial will follow the guidelines of Good Clinical Practice adapted for psychological treatment.

#### Procedure

We will start with recruitment of novice therapists (see below for details). Followed by a general training for all therapists in the basics of the treatment programs and routines. Here therapists learn to use the general therapist manual. After the general training a suitability testing of all therapists is performed to ensure that they have an adequate level of expertise in ICBT. After training therapists are randomized, 1:1 ratio, to either ICBT with DST or ICBT TRAD. The randomization is handled by an independent party (Karolinska Trial Alliance (KTA)) and will be on the therapist level. Separate, specific training of the two experimental groups, where both groups will be informed that they are in the “active” group. One group will be trained in how to use the DST and the other group will receive further training in the clinical routines and treatment structure (they will again be informed that this specific treatment structure and manual is what is being evaluated). Both groups receive a specific therapist manual adapted for DST or TRAD.

Recruitment and assessment of patients is done parallel to therapist recruitment and training. Randomization of patients is done to the two treatment arms, 1:1 ratio. After randomization patients receive 12 weeks of guided ICBT with a DST or guided ICBT TRAD. Patients answer online questionnaires at screening, pre-treatment, weekly measures during treatment, post-treatment and at follow-up assessment.

#### Participants and recruitment

Both therapists and patients are participants in this trial. The trial will consist of 10-40 novice therapists, primarily students in the final year of the 5-year clinical psychologist program, with basic education in CBT but little or no experience of ICBT. Each will treat 5-25 patients (total patient n=250 - 700).

The therapists will be recruited nationally in Sweden from different clinical psychologist programs thru advertising and contacts with key persons at these universities. If necessary additional therapists will be recruited among students who are finishing the two-year basic training program in CBT, plus among intern psychologists (‘PTP-psykolog’) at the psychiatric clinic at Psykiatri Sydväst in Stockholm. The patients will be recruited through the Internet Psychiatry Clinic routine intake plus through advertising on the web, for example on [www.studie.nu](http://www.studie.nu), and in traditional media.

A large number of ICBT studies have successfully used therapists with this level of competence. None of the therapists (or patients) will be aware of the randomization. Therapists are informed they will have the opportunity to learn ICBT within the context of a clinical trial evaluating slightly different versions of ICBT, and receive a diploma and in some cases a small monetary reimbursement or the possibility to take the course and treat the ICBT patients during office hours.

The patients in this setting will also be recruited nationally and assessed via internet and structured, diagnostic video- or telephone interviews according to well established procedures from previous ICBT-trials. Its content will mimic the assessment at the Internet Psychiatry Clinic.

*Inclusion criteria:*

- 18 years or older.
- Social anxiety, panic disorder or depression diagnosis.
- Stable or no antidepressant medication for at least 2 months.
- No diseases, disorders, or substance abuse that required other, immediate attention (e.g., severe depression or suicidality).
- Available time for treatment and acceptance of its format.
- Proficient in Swedish.
- No ongoing CBT.

*Exclusion criteria:*

- Not available for assessment and diagnostic telephone interview.
- Will not be in Sweden during the treatment period.
- Not able to receive text messages on a Swedish mobile phone.
- Not proficient in Swedish.
- No access to computer and internet.
- Not able to set aside about one hour a day to work on treatment.
- Bipolar disorder, if seeking depression treatment

All included patients will receive an ICBT-program for depression, social anxiety, or panic disorder. Patients log in to the secure, web based, online treatment platform to start the 12-week treatment program consisting of 10 modules. Every week patients receive a new module, read the text in the module, work on their own with exercises and work sheets. When a module is finished patients receive feedback and encouragement from their therapist through text messages. They can also ask questions to the therapist via text messages. When a module is finished the therapist assigns a new module. Therapists also monitor the patients' weekly symptom ratings to assess suicidality and large increases of symptoms.

All therapists receive a specific therapist manual, including recommendations of how much time to spend on each patient. Clinical psychologist with experience of ICBT will provide supervision via comments within the treatment platform and in weekly group format supervision via secure video conferencing, including only therapists from the same study arm. Therapists can also consult the supervisor by phone if necessary. Therapists continuously follow the therapist manual that they have been trained in during the introductory course. In the therapist manual all clinical routines and scenarios are described.

*Decision Support Tool (DST) group*

Therapists randomized to use the DST will have instructions on when and how to act on the feedback from the DST, for example by increasing intensity or type of support. The DST group will, mostly, during the first half of the treatment period receive guidance from the DST regarding the patient's expected final outcome which is defined as successful (the patient is either in remission, defined as below the previously established limit for diagnosis-

specific symptom scale and/or is a responder, i.e. has reduced symptoms by at least 50%) or failed (others). The primary indicators in the DST are colors that show that the patient's treatment is likely to be successful (green), likely to fail (red), very likely to fail (dark red), or that the prediction is too uncertain to say anything about the final outcome (yellow). In the case of red and green indicators, the therapist makes adjustments to the treatment based on clinical assessment, more detailed indicators in the DST and the specific manual that describes how the DST is to be interpreted. For red patients, it could for example be making a telephone assessment of the patient's problems and difficulties with the treatment, adapting parts of the content and how the treatment is given and providing more and/or other type of treatment support. Dark red means that the therapist, regardless of his or her own clinical assessment of the patient's situation, must make a telephone assessment and some form of adjustment. For green patients, the therapist is recommended to answer more concisely to messages from the patient, support the patient's independent work and monitor that the patient's progress remains good. The therapist's clinical assessment of what the patient needs may take precedence over these recommendations from the DST and the manual.

#### *Control group*

As described above the control group will also be included in teams with only therapists in the same experimental condition and receive a specific therapist manual with detailed instructions on how to guide patients through the treatment program and how to handle different clinical scenarios. Therapists will, through the manual and in supervision, be encouraged to assess how the patients are doing and to monitor their progress. As noted above they will be informed that they are in the active experimental group and that this study is evaluating the effect of their specific therapist manual and type of supervision. This procedure is expected to lower the risk that these therapists suspect they are in the control group.

#### *Statistical Analyses*

Primary analyses will be performed according to the intent-to-treat principle with Longitudinal Multilevel Modelling ('Mixed Models') or GEE including baseline covariates to control for non-random missingness. The power analysis is based on the primary hypothesis concerning differences in symptom reduction between DST and TRAD for patients being predicted to fail. Our previous proof-of-concept trial (13) shows that patients that during week four are predicted to fail and then receives enhanced ICBT increase their outcome (Cohen's  $d=0.53$ ) compared to those predicted to fail that stays on standard ICBT. To be conservative, we now estimate the effect the decision support tool to be  $d=0.40$ , which with a power of 80% and an data attrition of 20% would require 250 patients. Mainly because some secondary hypotheses are assumed to need more power and partly because the estimated effect is somewhat unsure and the design with randomization on the therapist level might can decrease power further (15), we will perform an interim, renewed power analysis after 250 patients have finished treatment. Depending on this analysis we can, if needed, include up to a total of 700 patients.

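### The primary population, patients predicted to fail, is set after randomisation and is not tied to a prediction made before the decision support tool can alter it

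*Protocol*

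**What the plan says.** **Who is compared.** Aim & Research questions, item 1, makes symptom reduction among patients predicted to fail the primary hypothesis. Statistical Analyses takes the same contrast for the power calculation: "differences in symptom reduction between DST and TRAD for patients being predicted to fail". The same section says that the primary analyses follow intent-to-treat.

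**When randomisation happens.** Under Procedure, "After training therapists are randomized, 1:1 ratio, to either ICBT with DST or ICBT TRAD", and "Randomization of patients is done to the two treatment arms, 1:1 ratio". Both steps precede the 12 weeks of treatment. Also, "Both groups receive a specific therapist manual adapted for DST or TRAD".

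**What the prediction uses.** According to Background, the algorithm was trained to "use data from baseline and early on in treatment (primarily week 1-4) to predict a patient's end state".

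**Who acts on it.** In the description of the DST group: "The DST group will, mostly, during the first half of the treatment period receive guidance from the DST". Red and green displays lead to adjustments, subject to clinical judgement. Dark red makes a telephone assessment and some adjustment mandatory. For green patients, shorter replies are recommended. In TRAD, predictions are made but not shown.

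**What is left open.** The protocol does not say which prediction (first, week four, any, last) or which colours put a patient in the primary population. Week four appears only in the account of the earlier proof-of-concept trial, where patients were classified first and then received enhanced treatment.

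**The concern.** Randomisation protects a comparison of everyone randomised, or of a subgroup whose membership the intervention cannot touch. Predicted failure is such a subgroup only if it is fixed before the DST has been acted on. After that, DST patients who have been helped may leave red, and green patients handled more briefly may enter it. The hidden TRAD predictions have no such feedback.

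The earlier trial that supplies the planning effect did not have this problem, because its classification came before the enhanced treatment. Here the DST may already have been at work by week four.

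The primary estimate is at stake. If the DST helps early, a later-defined red group in the DST arm holds the harder cases and the effect is understated. If briefer support pushes better-prognosis patients into red, the DST arm looks better than it is. While the rule is open, it could also be chosen after results are known.

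**Working it through.** **1. The plan's own figure.** Inputs from Statistical Analyses: d = 0.40, power 80%, attrition 20%. Two-sided 5% is assumed, since alpha is not stated.

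- Per arm: n = 2(1.96 + 0.84)²/0.40² = 98.1, rounded up to 99; total 198.
- With attrition: 198/0.80 = 247.5, rounded up to 248, against 250 stated. The figure reproduces.

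This is a count of patients in the compared population, so fixing the membership rule does not change it.

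**2. Illustration with two predictions.** The documents give none of the following inputs; all are assumptions:

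- symptoms at weeks 2, 4 and 12 are trivariate normal, with correlations 0.80 (weeks 2-4), 0.55 (2-12) and 0.65 (4-12);
- 50% are red at the first prediction (week 2), and everyone else counts as green;
- the DST improves week-12 outcome by 0.40 SD in first-prediction reds, and their week-4 score by 0.2 or 0.3 SD.

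With the group fixed at the first prediction, the week-12 SD among reds is √(1 − 0.55² × 2/π) = √0.807 = 0.90. So d = 0.40/0.90, about 0.44. Simulation with 4 million patients per arm gives the rest:

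| Selection rule | Red share, DST vs TRAD | Prognosis shift (DST worse) | d, late reds get full effect | d, late reds get 75% |
|---|---|---|---|---|
| First prediction | 50% vs 50% | 0.00 SD | 0.44 | 0.44 |
| Week 4, early gain 0.2 SD | 46% vs 50% | 0.04 SD | 0.42 | 0.39-0.40 |
| Week 4, early gain 0.3 SD | 43% vs 50% | 0.06 SD | 0.40 | 0.37 |
| Ever red | equal | 0.00 SD | 0.45 | 0.43 |

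From unrounded values, week-4 selection lowers d by about 5-11% when late reds get the full effect, and by 11-17% when they get 75%. The difference between those ranges is assumed shorter exposure, not selection.

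**3. The other direction.** Let briefer handling worsen green patients' week-4 scores by 0.2-0.3 SD and leave week-12 outcome unchanged for everyone. The true effect is then zero. Week-4 selection gives a spurious benefit of d = 0.06-0.09, ever-red selection 0.04-0.06, and first-prediction selection 0.00.

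**4. A second illustration with five predictions (weeks 2-6).** Assumed: about 40% red at any one prediction, an effect of 0.4 in reds, none in greens. Power is Φ(d√(n/2) − 1.96) with n = 100 evaluable per arm.

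| Rule | Share, DST vs TRAD | Prognosis shift | d | Power |
|---|---|---|---|---|
| First | 40.6% vs 40.6% | 0.00 SD | 0.385 | 78% |
| Week 4 | 37.6% vs 40.4% | 0.03 SD | 0.325 | 63% |
| Last (week 6) | 33.7% vs 40.6% | 0.07 SD | 0.27 | 48% |
| Ever red | 63.4% vs 63.4% | 0.00 SD | 0.325 | 63% |

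The ever-red row shows that part of each drop in d is shorter exposure, because its groups are balanced. The prognosis column is the selection part. Adding an assumed green effect of 0.2 unbalances ever red (65.3% vs 63.4%). With no DST effect at all, the groups match under every rule.

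**The case against.** **The protocol is silent rather than wrong, and the statistical analysis plan may settle the rule.** It names no later or any-time rule, and its text is compatible with using the first prediction. A reader might infer that the two groups certainly differ; the documents do not support that. It follows only for rules that use predictions made after DST output has been acted on. What remains is that the protocol itself states the primary population, builds the power calculation on it and calls the analysis intent-to-treat, in wording that admits rules breaking that principle.

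**Predictions may not be frequent, and not every display leads to action.** A reader might assume weekly predictions, but only the symptom measures are described as weekly. Action is mandatory for dark red alone, and clinical judgement may override the red and green advice. This limits the size of the feedback but does not remove it.

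**Any-time selection looks harmless.** In the illustrations it is nearly unbiased unless green handling turns some patients red. The protocol does recommend briefer replies to green patients, so that route is open.

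**There is no false positive if the DST does nothing.** This is correct. It does not cover a DST that changes interim scores without changing the final outcome (step 3).

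**Hypothesis 2 gives an unrestricted comparison.** It does, but it is not the primary hypothesis.

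**The first prediction is not perfect either.** It is less accurate, it changes the question for patients who turn red later, and arm-specific training and manuals act from the start of treatment. All of this stands.

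**Conclusion.** The concern holds in a limited form. The primary population is a post-randomisation subgroup that the intervention can alter, and the protocol does not anchor it to a prediction made before the DST is acted on. A later rule can select different patients in the two arms and weakens the intent-to-treat comparison.

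The selection bias is probably modest: about 0.04-0.06 SD of prognosis at week 4 in the first illustration and 0.03 SD in the second. It can understate the effect or, through green handling, create a small apparent benefit. The larger losses in d include assumed shorter exposure and should not be read as selection bias alone. Every size given here rests on assumed correlations, red shares and early effects. The direction of the argument rests only on the order of randomisation, prediction and action that the protocol describes.

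**What to change.** In Statistical Analyses, define the primary population by one prespecified prediction, made with the same locked algorithm and the same colour threshold in both arms, before any DST output is shown for that patient. State how yellow is classed. Then:

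- keep these patients in their randomised arm whatever colours appear later;
- report the predicted-to-fail share by arm as a check on balance;
- present ever-red or later-red selection, and the comparison of all randomised patients (hypothesis 2), as supportive;
- settle this before any outcome is examined by arm.

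The cost is one definition. Predictions are already made in both arms; that they are stored with their time points should be confirmed. The required number in the compared population stays at 248. The drawbacks are that an earlier prediction is less accurate, that patients who first turn red later count only in the supportive analyses, and that balance is close but not guaranteed because the arm-specific manuals act from the start. The change concerns the analysis only and leaves therapists' use of the DST as it is.

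### The 250 patients behind the stated 80% power are patients predicted to fail, but the protocol uses 250 as the minimum total enrolment and as the interim trigger

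*Protocol*

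**What the plan says.** The Aim & Research questions section marks larger symptom reduction among patients predicted to fail as the primary hypothesis. The Statistical Analyses section ties the power analysis to that hypothesis, namely "differences in symptom reduction between DST and TRAD for patients being predicted to fail". It takes d=0.40 as a cautious version of the d=0.53 seen in predicted-to-fail patients in the earlier insomnia trial, and concludes from this effect: "which with a power of 80% and an data attrition of 20% would require 250 patients".

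The number 250 then appears in two other roles:

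- Participants and recruitment, as the lower end of total enrolment: "Each will treat 5-25 patients (total patient n=250 - 700").
- Statistical Analyses, as the point at which a renewed power analysis is done, once 250 patients have completed treatment. Enrolment may then be extended to 700 in total.

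Neither place limits the count to patients predicted to fail. Patients are enrolled by diagnosis. The prediction comes later, mainly from baseline data and weeks 1-4 (Background). The description of the DST group has a green class (likely success) and a yellow class (too uncertain) as well as red and dark red.

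**The concern.** A sample size derived for a subgroup has been carried over as the size of the whole trial. Patients classed green or yellow add to the total but not to the primary contrast. If any appreciable part of the sample falls in those classes, 250 enrolled patients cannot deliver the stated 80% for the primary hypothesis.

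Two decisions rest on the number. One is the minimum size of the trial. The other is the timing of the renewed power analysis, which would take place with fewer primary-population patients than the calculation assumed. This is the only sample-size justification the protocol gives for its primary hypothesis.

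**Working it through.** **Inputs**

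- Effect d = 0.40, power 80%, attrition 20% (Statistical Analyses).
- Allocation 1:1 (Procedure): "Randomization of patients is done to the two treatment arms, 1:1 ratio".
- Alpha and sidedness are not stated. Two-sided 5% is assumed, because it reproduces 250. A one-sided 5% test would need 78 per arm, and 156/0.8 = 195.
- Share predicted to fail, f: not stated. As an illustration only, the Background's range for CBT in general, "30-60% of patients end up as non-responders", is used for f. A wider range is shown below.

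**Step 1: reproduce the plan's figure.** A two-sample t-test at d = 0.40, two-sided 5%, 80% power needs 99.1 per arm, rounded up to 100 (power 80.4%). Two arms give 200, and allowing for attrition 200/(1 − 0.20) = 250, exactly the protocol's number. The normal approximation gives 99 per arm, 198 in total, and 198/0.8 = 247.5, rounded up to 248. The step from 200 to 250 is accounted for by attrition alone. Nothing is left over for the predicted-to-fail share or for therapist clustering.

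**Step 2: power when 250 or 700 is the total.** With N enrolled, the analysed number per arm in the primary population is

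n = N × f × 0.8 / 2.

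At N = 250 this is 100f, and at N = 700 it is 280f. Power is by t-test at d = 0.40. The last column is 250/f, the enrolment that would be expected to yield 250 patients predicted to fail.

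| f | n per arm, N=250 | Power, N=250 | n per arm, N=700 | Power, N=700 | 250/f |
|---|---|---|---|---|---|
| 30% | 30 | 33% | 84 | 73% | 833 |
| 40% | 40 | 42% | 112 | 85% | 625 |
| 50% | 50 | 51% | 140 | 92% | 500 |
| 60% | 60 | 58% | 168 | 96% | 417 |
| 100% | 100 | 80% | 280 | over 99% | 250 |

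Outside the illustrative range, power at N = 250 is about 23% at f = 20% and 71% at f = 80%.

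**Step 3: when 700 is enough.** 700 × f = 250 gives f = 250/700 = 35.7%. From a share of about 36%, the maximum enrolment supports 80% power, before clustering.

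**Step 4: detectable effect at N = 250.** For 80% power, 60 analysed per arm (f = 60%) can detect d of about 0.52, and 30 per arm (f = 30%) about 0.74. The planning value is 0.40.

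**Step 5: what the interim would see.** At 250 patients in total, the primary population would number 250 × 0.30 = 75 to 250 × 0.60 = 150, against the 250 that the calculation requires.

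**The case against.** The arithmetic linking 250 to the predicted-to-fail group is not in dispute, and no text in the protocol scales it for the share. Three points limit how far the criticism goes.

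**250 is a floor.** The protocol plans a renewed power analysis and allows up to 700 patients. That review could reveal a small predicted-to-fail group, and at 700 the illustrative shares give 73-96%. This stands as mitigation. It does not remove the error: the reasons given for possibly going beyond 250 are secondary hypotheses, an unsure effect and therapist-level randomisation. The subgroup restriction is not among them, extension is optional, and nothing ties it to the number predicted to fail.

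**The 30-60% is not the tool's share.** It describes non-response to CBT in general, whereas failure here means neither response nor remission. The yellow class could make the flagged share smaller. Guidance is given over several weeks, so a rule counting anyone ever flagged red could make it larger. This stands, and every power figure that uses the range is conditional on it. The core point does not need the range: by the t-test, no share below 100% gives the stated 80% at 250 in total.

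**The planned analysis is not a t-test.** The protocol plans mixed models or GEE with baseline covariates. If d is on the raw-SD scale, adjustment raises power. With an assumed baseline-outcome correlation of 0.5, d becomes 0.40/√(1 − 0.25) = 0.46, and power at 250 is 42-71% over the same shares. A correlation of about 0.63 (share 60%) or 0.70 (share 50%) would give about 80%. No correlation is stated, and the exact match in step 1 makes the unadjusted calculation the likeliest origin of 250. Therapist clustering, also absent from the 250, works in the other direction, as the protocol itself recognises.

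**Conclusion.** The point holds as an error in what the protocol states. The 250 is the number of predicted-to-fail patients needed for 80% power at d = 0.40 with 20% attrition (two-sided 5% assumed), yet it serves as the minimum total enrolment and as the interim trigger for patients of any prediction.

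Two stronger readings are tempting and are not supported:

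- A reader might infer that the trial has only 33-58% power for its primary hypothesis. That range requires both stopping at 250 and a flagged share of 30-60%. The protocol commits to neither.
- A reader might infer that the 700 ceiling is inadequate. It falls short of 80% only below a share of about 36% (73% at 30%), and the share is unknown from this document.

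All these figures leave out therapist clustering, which lowers power, and covariate adjustment, which may raise it.

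**What to change.** In Statistical Analyses:

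1. State that 250 is the number of randomised patients predicted to fail required for the primary hypothesis, and state the alpha and sidedness used.
2. Give the expected predicted-to-fail share. The 5500 historical patients used to train the prediction model offer a direct estimate.
3. Replace the implied 80% at 250 in total with the power, or the detectable effect, at both 250 and 700 in total under that share.
4. Base the renewed power analysis on the number of predicted-to-fail patients who have finished treatment.

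In Participants and recruitment, keep the 250-700 range but make clear that it counts all patients.

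Keep the 700 ceiling and state the power it gives. Requiring 250/f patients in total would be a larger change: it means 417-833 patients over the illustrative shares, and conflicts with the ceiling below a share of about 36%.

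The cost is rewording and a less favourable stated power at 250. No new trial procedures are needed. If the corrected figures lead the sponsor to enrol more patients within the existing ceiling, that recruitment effort is a further cost.
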